### Usual care

The services and interventions available to people with dementia and family carers randomised to receive usual treatment will vary between and within centres and over time. In principle all the interventions offered to this group will also be available to those in the active treatment groups as we are evaluating the *additional *effects of reminiscence work. The only exception to this is when reminiscence groups occur at the same time as an alternative intervention. Our commitment to costing services and interventions received allows us to monitor whether control groups are receiving alternative interventions in this way. Though changes and developments in the availability of medications for Alzheimer's and other dementias should affect both groups equally, we intend to monitor this through the costing information we collect.

Participants in the usual treatment group may well engage in some form of reminiscence work during the 10 months of the study period. This is a popular approach in day-care centres, and reminiscence materials are widely available. However it is unlikely that structured reminiscence work will be offered in any of the centres, and even less likely that it will be offered jointly to carers. It is this systematic group-based approach, rather than a general exhortation to reminisce to improve communication, that is the focus of this evaluation.

### Ethical arrangements

#### Risks and anticipated benefits for trial participants

There appear to be no documented harmful side-effects from participating in reminiscence groups and no adverse reactions were apparent in the MRC trial platform. Some past memories can be unhappy, and even traumatic, but with a skilled and trained facilitator participants will share only those aspects they feel comfortable with, and if distressing memories were to surface, the person would be given additional support on a one-to-one basis.

Benefits are consistently reported by participants in the groups, including enjoyment, feelings of validation and self-worth. The desire of participants to continue meeting following the sessions provides an indication of the value placed on the benefits. Prospective participants will be fully informed of the potential risks and benefits of the project.

Nevertheless, a reporting procedure is in place to ensure that serious adverse events are reported to the Chief Investigator. Upon becoming aware of an adverse event involving a participant or carer, a member of the research team assesses whether it is "serious". A Serious Adverse Event (SAE) is defined in the trial as an untoward occurrence experienced by either a participant or carer which:

• results in death;

• is life threatening;

• requires hospitalisation or prolongation of existing hospitalisation;

• results in persistent or significant disability or incapacity;

• is otherwise considered medically significant by the investigator;

• falls within the scope of the Protection of Vulnerable Adults (POVA) protocol which is in place to ensure that suspected cases of abuse or neglect are followed-up in an appropriate manner.

A reporting form is submitted to the CI who assesses whether the SAE is:

• related to the conduct of the trial;

• unexpected.

SAEs that are judged to be related and unexpected are reported to MREC and the trial DMEC within 15 days.

#### Consent

Participants will be in the mild to moderate stages of dementia, and therefore would generally be expected to be competent to give informed consent for participation, provided that appropriate care is taken in explaining the research and sufficient time is allowed for them to reach a decision. In every case, the participant will have had at least 24 hours to consider the information provided. It is helpful for a family member or other supporter to be involved, and we would aim to ensure that this is done wherever possible. Informed consent will be sought separately from the family care-giver, in relation to their own participation. It will be made clear to both participants and family care-givers that no disadvantage will accrue if they choose not to participate.

In seeking consent, we will follow current guidance from the British Psychological Society on evaluation of capacity. In this context, consent has to be regarded as a continuing process rather than a one-off decision, and willingness to continue participating will be continually checked through discussion with participants during the assessments.

Where the participant's level of impairment increases, so that they are no longer able to provide informed consent, the provisions of the Mental Capacity Act will be followed, with the family care-giver as consultee. Where the person has themselves given informed consent initially, this provides a clear indication of the person's likely perspective on continuing at later time-points. The same procedure will apply where the person with dementia appears to lack capacity to consent initially, but meets the other criteria for the project. At any point where a participant with dementia becomes distressed by the assessments they will be discontinued.

### Outcome measures

Primary and secondary measures are completed at baseline, three months after baseline (first follow-up) and ten months after baseline (second follow-up and primary end-point). The interviews for the first follow-up are conducted after the completion of the weekly RYCT sessions, while the interviews for the second follow-up are scheduled after the final monthly maintenance session.

#### Primary outcome measures

a) Quality of life of the person with dementia, using the scale *Quality of Life in Alzheimer's Disease *(QoL-AD) [19], which covers 13 domains of quality of life. This is reliable and valid for people with mild and moderate degrees of dementia when they take part in structured interviews with trained interviewers [20,21].

b) Care-giver's mental health, assessed using the 28-item, self-completed *General Health Questionnaire *GHQ-28 [22] which has been widely used in care-giver research [23,24]; we shall use four-point Likert scales ranging from zero to three. The questionnaire includes indicators of anxiety, depression, insomnia, social dysfunction and somatic symptoms. We chose the GHQ-28 over the Relatives' Stress Scale because it is more general and more widely used.

#### Secondary outcome measures

a) Autobiographical memory, assessed using an extended version of the *Autobiographical Memory Interview *(AMI) [25]. The extended AMI assesses the person with dementia's recall of personal memories relating to both factual (semantic) information (for example, names of schools or teachers) and specific incidents. In the trial platform, we validated an additional section covering the period from middle-age to retirement, to cover the life-span of our participants.

b) Quality of relationship, assessed by both person with dementia and carer using the *Quality of the Carer-Patient Relationship *(QCPR) [26]. Originally developed in Belgium this scale comprises 14 items with 5-point Likert scales designed to assess the warmth of the relationship and the absence of conflict and criticism. In the trial platform the QCPR had good internal consistency for carers (α = 0.85) and for people with dementia (α = 0.80), and concurrent validity with other measures of relationship quality and carer stress.

c) Depression and anxiety, using *Cornell Scale for Depression in Dementia *(CSDD) [27] and *Rating Anxiety In Dementia *(RAID) [28] for person with dementia; and *Hospital Anxiety and Depression Scale *(HADS) [29] for carer. The CSDD is a 19-item scale, derived from interviews with the people with dementia and their carers in which the interviewer describes signs and symptoms to the carer. Where there is a discrepancy between carer's and clinician's ratings, the interviewer re-interviews the carer before making a final judgment. The RAID is an 18-item scale to rate anxiety in people with dementia based on structured interviews with them and their carers. The HADS is a well-validated 14-item, self-completed scale that measures both anxiety and depression, and is suitable for use with adults of all ages.

d) Stress specific to care-giving, using the *Relative's Stress Scale *[30], which asks the care-giver to complete 15 5-point Likert items.

e) Quality of life of person with dementia, rated by the care-giver using the proxy version of the *QoL-AD *[19], identical in structure and content to the version completed by the person with dementia.

f) General quality of life of both care-giver and person with dementia, using *EQ-5D *[31]. This is a standard measure of health-related utility, applicable to all health conditions. It provides a simple health profile and a single value for health status designed to calculate Quality Adjusted Life Years (QALYs). Care-givers will complete the measure from their own perspective and for the person with dementia, who will also complete it whenever possible.

g) Functional ability of person with dementia, using the *Bristol Activities of Daily Living Scale *[32], a 20-item scale completed by the carer.

h) Costs, using the validated *Client Services Receipt Inventory *(CSRI) [33]. Used extensively in studies of mental health and dementia (e.g. [34]), this gathers comprehensive data on accommodation, medication and services received. In this trial the data will reflect either the previous three months (at baseline and after treatment) or seven months (at follow-up).

#### Sample size

Our target sample size is 400 patients completing data collection for the trial after ten months, comprising 200 randomised to attend reminiscence groups and 200 receiving treatment as usual. In the trial platform intra-class correlation coefficients (ICCs) within randomised groups were often negative, but never significantly greater than zero, for both the carer-specific GHQ-28 and the carer-rated QoL-AD. However they were close to 0.1 for the QoL-AD rated by the person with dementia. Using a 5% significance level, therefore, comparison of the 200 pairs completing the intervention with the 200 pairs receiving treatment as usual will yield 80% power of detecting a standardised difference of 0.28 in carer-specific GHQ-28 or carer-rated QoL-AD. In contrast the patient-rated QoL-AD is likely to suffer a 'variance inflation factor' of approximately 1.74 [viz. 1 + 0.1 × (average completed group size of 8.4 minus 1)], thus yielding a power of 80% of detecting a standardised difference of 0.38. Our trial platform, which had a sample size of 57 in 3 centres, suggests that standardised differences of 0.28, even 0.38, are plausible. In our judgement they also fall within the range of clinically important effects. Furthermore, because our trial platform was exploratory, and therefore more heterogeneous than the proposed definitive trial, ICCs and standard deviations are likely to fall. To achieve a sample size of approximately 400, we allow for 12% attrition between recruitment and the post-treatment assessment (estimated from our trial platform) and a further 18% attrition over the following 7 months (estimated from a community study [35]). Hence we seek an initial sample size of 576, requiring 24 treatment groups initially comprising 12 pairs and another 288 pairs randomised to usual treatment.

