**Design and methods:**

This multi-centre, pragmatic randomised controlled trial (RCT) to assess the effectiveness and cost-effectiveness of joint reminiscence groups for people with dementia and their family care-givers has two parallel arms – an intervention group and a control group who receive care as usual. The intervention consists of joint reminiscence groups held weekly for twelve consecutive weeks, followed by monthly maintenance sessions for a further seven months.

The primary outcome measures are the quality of life of people with dementia, as assessed by QoL-AD, and their care-givers' mental health as assessed by the GHQ-28. Secondary outcomes include: the autobiographical memories of people with dementia; the quality of the relationship between them and their care-givers; and the levels of depression and anxiety felt by them and their care-giver. Using a 5% significance level, comparison of 200 pairs attending joint reminiscence groups with 200 pairs receiving usual treatment will yield 80% power to detect a standardised difference of 0.38 in the QoL-AD rated by the person with dementia and 0.28 in the GHQ-28 or carer-rated QoL-AD. The trial will include a cost-effectiveness analysis from a public sector perspective.

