## Design and methods

### Design

The design is a pragmatic eight-centre randomised trial (Figure 1). After selection, and baseline assessment, pairs of people with dementia and their family carer are randomised to one of two groups; the intervention group receives usual care plus joint reminiscence groups and reminiscence-based maintenance, the control group receives usual care only. Participants are free to seek additional assistance and support elsewhere at any time after baseline. Participants are allowed to enter the study only after giving signed informed consent in accordance with the provisions of the Mental Capacity Act 2005 [18]. General ethical approval was obtained through the Multi-centre Research Ethics Committee for Wales (ref no. 07/MRE09/58). The study is registered as a clinical trial with ISRCTN 42430123.

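### The 80% power quoted at 0.38 for patient-rated QoL-AD implies group clustering in both arms; with groups in the intervention arm only, the plan's own inputs give about 0.33 to 0.34

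*Protocol article*

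**What the plan says.** The Sample size section of the Protocol article aims for 400 completers at ten months, "comprising 200 randomised to attend reminiscence groups and 200 receiving treatment as usual". It gives two detectable differences.

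- **GHQ-28 and carer-rated QoL-AD.** Intra-class correlations (ICCs) in the trial platform were often negative and "never significantly greater than zero, for both the carer-specific GHQ-28 and the carer-rated QoL-AD". The 200 v 200 comparison "will yield 80% power of detecting a standardised difference of 0.28 in carer-specific GHQ-28 or carer-rated QoL-AD".
- **Patient-rated QoL-AD.** The ICC was close to 0.1. The section forms a variance inflation factor of 1.74 from that ICC and an "average completed group size of 8.4 minus 1", "thus yielding a power of 80% of detecting a standardised difference of 0.38". The Abstract repeats that the comparison "will yield 80% power to detect a standardised difference of 0.38 in the QoL-AD rated by the person with dementia".

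On the structure of the arms, the Design section says that "the intervention group receives usual care plus joint reminiscence groups and reminiscence-based maintenance, the control group receives usual care only". The Sample size section counts 24 treatment groups of 12 pairs and a further 288 pairs on usual treatment, with no groups mentioned for the latter. Under Randomisation, pairs are randomised in batches of up to 24, and the 12 allocated to intervention attend the sessions. The statistical analysis section plans a multi-level model for clustering within groups as randomised, without naming the arm.

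**The concern.** The factor of 1.74 uses the completed size of a reminiscence group: 12 pairs less 30% attrition (12% + 18%), so 12 × 0.70 = 8.4. That is a feature of the intervention arm. Controls are randomised as individual pairs and never meet as a group, so nothing in the document gives their outcomes a comparable within-group correlation. This is a partially nested design, and the inflation belongs to one arm's variance.

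If both arms are inflated, the stated detectable difference is too large and the stated power at 0.38 too low. At stake is the accuracy of the published power statement for one of the two primary outcomes. Readers would believe that the trial can only detect a larger QoL-AD effect than it can on its own assumptions.

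**Working it through.** **Inputs.** From the Sample size section: 5% significance, 80% power, 200 completers per arm, ICC 0.1, completed group size 8.4, 24 treatment groups. Sidedness is not stated; two-sided is assumed because it reproduces the 0.28. Outcomes are standardised (SD = 1).

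**Formula.** Detectable difference = (1.960 + 0.842) × √V = 2.802 × √V, where V is the variance of the difference in means. Power at a difference d = Φ(d/√V − 1.960).

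**Step 1: the plan's figure without clustering.** V = 2/200 = 0.0100, so 2.802 × 0.1000 = 0.280. This matches the stated 0.28 and confirms the significance level and sample size used.

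**Step 2: the inflation factor.** 1 + 0.1 × (8.4 − 1) = 1.74, as stated.

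**Step 3: the plan's 0.38, with 1.74 in both arms.** V = (1.74 + 1.74)/200 = 0.0174, √V = 0.1319.

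- Normal approximation: 2.802 × 0.1319 = 0.370; power at 0.38 is 82.1%.
- t-test with 24 clusters in each arm (2 × 24 − 2 = 46 df): 0.377, which rounds to 0.38; power at 0.38 is 80.5%.

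So the stated figure reproduces, provided both arms are treated as clustered.

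**Step 4: the design described, with 1.74 in the intervention arm only.** V = (1.74 + 1)/200 = 0.0137, √V = 0.1170.

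| Method | Difference at 80% power | Power at 0.38 |
|---|---|---|
| Normal approximation | 0.328 | 90.1% |
| t, Satterthwaite df ≈ 55 | 0.334 | 89.1% |
| t, 23 df (24 groups − 1, most cautious) | 0.342 | 87.5% |

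The normal row is Φ(0.38/0.1170 − 1.960) = Φ(1.287) = 0.90. The Satterthwaite df is 2.74² / (1.74²/23 + 1²/199) ≈ 55.

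**Step 5: sensitivity, one arm inflated, normal approximation.**

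- Group variance added on top of an individual variance of 1 (intervention total 1/0.9): V = (1.74/0.9 + 1)/200, giving 0.339 and 88.1% power at 0.38.
- Intervention total variance 1, control variance 0.9: V = (1.74 + 0.9)/200, giving 0.322 and 91.1%.
- Unequal completed group sizes, assumed coefficient of variation 0.4: factor 1 + 0.1 × (1.16 × 8.4 − 1) = 1.874, giving 0.336.
- ICC 0.05 gives 0.305 and 93.7%; ICC 0.15 gives 0.349 and 86.2%.

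None of these returns to 80% power at 0.38. Expressed as completers per arm for 0.38 at 80% power (normal approximation), both arms inflated needs 190 and one arm inflated needs 149.

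**The case against.** **The text never says that both arms were inflated.** True: it is an inference from the number. It is a firm one, because intervention-only inflation misses 0.38 in every variant above.

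**The authors may have meant it.** The document speaks of groups as randomised rather than treatment groups, and batches of up to 24 are split into halves. The control half of each batch could have been treated as a cluster, as a cautious planning choice. This does not rescue the figure. A centre, wave or batch effect common to both halves largely cancels in the comparison between arms, while an effect of sharing a therapy group arises in one arm only. Neither gives 1.74 among controls. If there is another reason for control clustering, the document does not give it.

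**The error is harmless.** Largely so. At least 80% power at 0.38 remains true, the sample size need not change, and the completed trial will be judged on its estimate and confidence interval. That limits the weight of the point without making the stated pairing correct.

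Three stronger readings are tempting and not supported:

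- *That the trial is underpowered for QoL-AD.* The error runs the other way.
- *That 0.38 is a slip because 0.280 × √1.74 = 0.37.* A standard allowance for 46 df gives 0.377, so the figure follows from the method implied.
- *That the 0.28 for GHQ-28 is wrong because carers share the same groups.* It is correct at the planning ICC of zero. The document's basis for zero includes often-negative estimates as well as non-significance, and it gives no positive ICC for this outcome. Any loss of power would rest on hypothetical ICCs.

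**Conclusion.** The concern holds for patient-rated QoL-AD. On the plan's own inputs and the design it describes, 200 v 200 completers give 80% power for a standardised difference of about 0.33 to 0.34, depending on degrees of freedom, and about 87% to 90% power at 0.38. The stated 0.38 overstates the detectable difference by about 0.04 to 0.05.

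This rests on a two-sided 5% test, an ICC of 0.1 arising from shared reminiscence groups, equal total variance in the two arms and an average completed group size of 8.4. Relaxing the variance or group-size assumption moves the detectable difference only between 0.32 and 0.34. The conclusion would change if there were a documented reason for comparable clustering among controls. The figure for GHQ-28 and carer-rated QoL-AD stands as stated.

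**What to change.** Keep the recruitment target of 576. In the Sample size section, apply the factor of 1.74 to the intervention arm only, with variance (1.74 + 1)/200. Restate the patient-rated QoL-AD figure as about 0.33 to 0.34 at 80% power, or equivalently about 87% to 90% power at 0.38, and name the degrees of freedom used. Make the same change in the Abstract. If the sponsor prefers to keep 0.38, state that both arms were inflated and why controls should be clustered.

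For consistency, add to the statistical analysis section that the multi-level model carries the group effect in the intervention arm only. A range of GHQ-28 detectable differences by ICC would be an optional sensitivity analysis, not a correction.

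The cost is a sentence or two in the methods and one in the Abstract, with no change to participants, outcomes or timetable.

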### Analysis

#### Statistical Analysis of Effectiveness

We shall analyse by intention to treat and include all available data. However methods of imputing missing data such as last observation carried forward (LOCF) are of limited utility in dementia, where the norm is gradual decline until loss through death and illness. Hence our sample size calculations are based on the numbers we expect to be available at the study end-point, ten months after randomisation. We shall use multi-level modelling to address clustering within randomised groups. We shall use analysis of covariance to adjust for baseline differences in outcome variables. Analyses will treat ten months after randomisation as the primary end-point in evaluating whether the intervention has affected people with dementia or their care-givers. Secondary analyses will focus on effects immediately after the intensive group sessions.

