### Participants

Recruitment to this trial is taking place through mental health services for older people in each area (especially Memory Clinics, Community Mental Health Teams for Older People and associated professionals including psychiatrists, occupational therapists and Admiral Nurses), associated day services and through relevant local voluntary sector agencies such as the Alzheimer's Society and Age Concern. Recruitment will be in three waves, giving centres the opportunity to focus on different geographical areas in different waves. The Appendix sets out the inclusion and exclusion criteria for participants in the trial.

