### Randomisation

Local researchers, who do not take part in follow-up assessments, contact the remote randomisation service of the North Wales Organisation for Randomised Trials in Health (NWORTH) when they have up to 24 pairs ready for randomisation. NWORTH is accredited as a Clinical Trials Unit by the UK Clinical Research Collaboration (UKCRC) and funded by the Clinical Research Collaboration Cymru, notably for HTA trials. The same researcher arranges for the 12 pairs randomised to the intervention group to attend sessions, and liaises with the group facilitator.

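### The effectiveness analysis names one clustering level, but allocation is within batches shared by both arms and only the intervention arm meets in groups; a model with that level alone is conservative, as is the stated 0.38.

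*Protocol article*

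**What the plan says.** The section Statistical Analysis of Effectiveness deals with clustering in one sentence: "We shall use multi-level modelling to address clustering within randomised groups". It adds analysis of covariance on the baseline score. It mentions no centre, wave or batch term, and does not say whether control pairs carry a group effect.

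Other sections describe the layout:

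- Design: "The design is a pragmatic eight-centre randomised trial".
- Participants: "Recruitment will be in three waves, giving centres the opportunity to focus on different geographical areas in different waves".
- Randomisation: pairs are submitted in batches of up to 24, and "The same researcher arranges for the 12 pairs randomised to the intervention group to attend sessions".
- Intervention and Usual care: intervention pairs attend facilitated groups of at most 12 pairs; control pairs attend no trial group.
- Sample size: 24 treatment groups of 12 pairs plus 288 control pairs, and a completed sample "comprising 200 randomised to attend reminiscence groups and 200 receiving treatment as usual". With no clustering this gives "80% power of detecting a standardised difference of 0.28 in carer-specific GHQ-28 or carer-rated QoL-AD". For patient-rated QoL-AD, the platform ICC was near 0.1. The article computes an inflation of 1.74 from an average completed group of 8.4, "thus yielding a power of 80% of detecting a standardised difference of 0.38".

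**The concern.** Two sources of correlation follow from this layout, and they act differently. The batch (a centre in a wave) is shared by both arms, so its effect cancels from a within-batch treatment comparison. The reminiscence group exists only in the intervention arm, so its effect does not cancel.

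The article names one level and uses the same term in the sample-size section for sets averaging 8.4 completers. Since 12 × 0.70 = 8.4, the natural reading is the 12-pair set in each arm, not the batch of 24. A model with only that level has no term for what the two arms of a batch share. It also gives control pairs a group structure that they do not have.

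At stake are the precision of the patient-rated QoL-AD comparison and the accuracy of its planning figure. Batch variation is plausible on the article's own account: waves may cover different areas, and usual care is said to vary between and within centres and over time.

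**Working it through.** **Inputs from the article.** 200 completers per arm; 5% significance (two-sided assumed); 80% power; ICC 0.1 for patient-rated QoL-AD; completed group size m = 8.4; 24 treatment groups.

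**Assumed.** 24 equal batches (8 centres × 3 waves = 24, inferred; it matches the 24 groups). Batch ICC b from 0 to 0.10. Total variance 1 in each arm, and no gain from baseline adjustment.

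**1. Reproducing the stated figures.** z₀.₉₇₅ + z₀.₈₀ = 2.802.

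- No clustering: 2.802 × √(2/200) = 0.280. This agrees with 0.28.
- Inflation: 1 + 0.1 × 7.4 = 1.74. In both arms, the normal formula gives 2.802 × √(2 × 1.74/200) = 0.370. With t on 46 degrees of freedom (24 + 24 − 2), 2.862 × 0.1319 = 0.378. So 0.38 reproduces when both arms are treated as clustered.

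**2. Inflating the intervention arm only.**

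- Equal total variance in the arms: 2.802 × √((1.74 + 1)/200) = 2.802 × 0.1170 = 0.328.
- Group variance added on top of the control variance (intervention variance 1/0.9): 2.802 × √((1.74/0.9 + 1)/200) = 2.802 × 0.1211 = 0.339.
- Power at 0.38 in the first case: Φ(0.38/0.1170 − 1.96) = about 90%.
- These use normal quantiles, so the like-for-like both-arm figure is 0.370. With t on 23 degrees of freedom (multiplier 2.926), the two results are 0.343 and 0.354, to set against 0.378. The both-arm figure is conservative on either scale.

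**3. Single 12-pair level in both arms, batch omitted.** Let g be the group ICC, in the intervention arm only.

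- True variance of the treatment difference = T/24, with T = g + (2 − 2b − g)/m.
- Variance the model reports = (T + 2b)/24, because the shared batch variance is counted once in each arm.
- Model SE / true SE = √(1 + 2b/T).

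| b | g | T | SE ratio | approx. type I error |
|---|---|---|---|---|
| 0 | 0.10 | 0.326 | 1.00 | 5.0% |
| 0.05 | 0.05 | 0.270 | 1.17 | 2.2% |
| 0.05 | 0.10 | 0.314 | 1.15 | 2.4% |
| 0.10 | 0 | 0.214 | 1.39 | 0.6% |

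The ratio is never below 1. The first row shows that giving controls a group effect is neutral by itself in this balanced layout.

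**4. The other reading: one intercept per batch of 24, no therapy-group term.** At b = 0, g = 0.10:

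- Within-cell residual variance, averaged over arms: (0.9 + 1)/2 = 0.95, on 48 × 7.4 = 355.2 degrees of freedom.
- Batch-by-arm mean square: (8.4/2) × 0.326 = 1.37, on 23 degrees of freedom.
- Pooled residual: (355.2 × 0.95 + 23 × 1.37)/378.2 = 0.976.
- Model SE / true SE = √((2 × 0.976/8.4)/0.326) = 0.84, so type I error is about 10%. At g = 0 the ratio is 1.00.

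**The case against.** The strongest reply is that this is a condensed article. It commits to multi-level modelling and baseline adjustment, does not say that only one level will be fitted, and excludes no centre or batch term. Random-effect structure and degrees of freedom commonly go to the analysis plan, which is not shown. This stands as far as it goes: the article does not name the batch, which is not the same as deciding to leave it out. It does not cover the sample-size section, which states a figure that reproduces only if untreated controls are clustered like the intervention arm. Nor does it cover a term that is used in the analysis without a definition.

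Other limits also stand. The 24 equal batches are inferred, since the Randomisation section says up to 24 pairs. No batch ICC is given. Baseline adjustment may absorb part of the batch variation.

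Three stronger readings are tempting, and the article supports none of them.

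- A reader might infer that leaving out the batch makes false positives more likely. It does the reverse (working, step 3). Standard errors that are too small need the batch-only reading in step 4, which fits badly with a group size of 8.4.
- A reader might infer that both primary outcomes are shown to be affected. The 0.1 ICC belongs to patient-rated QoL-AD. For GHQ-28 the platform ICCs were often negative and never significantly above zero.
- A reader might apply the 0.1 ICC to a difference of 0.28 and report a large loss of power. That difference is the target for outcomes with ICCs near zero; the target for patient-rated QoL-AD is 0.38. If the whole 0.1 is batch variance (model SE √(0.414/24) = 0.131, true SE √(0.214/24) = 0.094), power at 0.38 is Φ((0.38 − 2.013 × 0.131)/0.094), about 89%. That is above the planned 80%, against about 97% with the batch modelled.

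**Conclusion.** The point holds as a matter of efficiency and clarity. On the natural reading, a model with the 12-pair level alone gives standard errors about 0% to 39% too large for a batch ICC of 0 to 0.10. That range is an assumption, and baseline adjustment would narrow it. Validity is threatened only if the term means the batch of 24 and no therapy-group effect is fitted; type I error for patient-rated QoL-AD would then be about 10% at a group ICC of 0.1. The undefined wording does not rule that out.

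The stated detectable difference of 0.38 is conservative. With inflation in the intervention arm only it is about 0.33 (0.33 to 0.34 by the normal formula; 0.34 to 0.35 on 23 degrees of freedom). No effect on GHQ-28 is demonstrated.

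**What to change.** 1. Define the clustering term: say whether it means the batch of up to 24 or the reminiscence group of up to 12, and state that control pairs carry no group effect.
2. Specify the model for each primary outcome as arm + baseline score + centre-wave batch (both arms) + a random effect for reminiscence group in intervention pairs only, with small-sample degrees of freedom.
3. Restate the patient-rated QoL-AD detectable difference with inflation in the intervention arm only, giving the variance convention and the degrees of freedom used.

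The cost is analysis wording. Randomisation and group attendance already generate the batch and group identifiers, and recruitment does not change. The downside is fewer denominator degrees of freedom, about 23 rather than 46. This raises the two-sided 5% critical value from about 2.01 to 2.07, so if batches differ little the test gives up a little power.
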